### Outcome Measures

#### Primary Outcome Measure

Assessments will be conducted before the start of the intervention, after the 7-week program, and at the 4-week follow-up (Figure 3). Data collection will be conducted in person at the UDESC facilities for both the face-to-face and home-based groups. In the initial assessment, a characterization questionnaire will be administered to obtain socioeconomic and health information (age, marital status, educational level, occupation, PA level, and main symptoms). Patient data will be maintained solely by the principal researcher to protect confidentiality throughout the study, from inception to conclusion. The variables analyzed, along with their respective instruments, are listed below.

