**Objective:**

This study protocol aims to compare the effectiveness of a home-based prehabilitation program with a face-to-face prehabilitation program on physical and psychological variables in individuals with severe obesity awaiting BMS.

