### Eligibility Criteria

Individuals of both genders with grade III (severe) obesity who meet the following criteria will be included in the research: (1) BMI>40 kg/m^2^, (2) indication for BMS, (3) formal indication for preoperative physical therapy signed by the BMS surgeon, in accordance with the multidisciplinary guidelines for BMS, (4) absence of comorbidities that compromise safety or the ability to perform the exercises and functional tests, and (5) no participation in any structured exercise program in the past 3 months. To ensure equitable access and diversity, recruitment will be stratified to achieve a sample composition of 50% low-income individuals (defined as monthly household income per capita ≤0.5 minimum wage or total household income ≤3 minimum wages) and 20% residents of rural areas. In addition, participants will be excluded if they meet any of the following criteria: (1) presence of a pacemaker, history of myocardial infarction within the previous 3 months, or unstable angina pectoris; (2) sustained or episodic cardiac arrhythmias aggravated by PA, symptomatic peripheral vascular disease, or any clinical condition representing a risk (eg, inability to safely tolerate heart rate increases >20 beats/min during exercise); (3) clinical diagnosis of acute or chronic respiratory diseases that compromise the safety of physical tests (eg, COPD and asthma with remodeling) or peripheral oxygen saturation (SpO₂) <92% during the 6-minute walk test (6MWT); (4) history of previous BMS or abdominal or thoracic surgery within the previous year; (5) abusive use of or chemical dependence on psychoactive substances (including alcohol and illicit drugs), according to clinical criteria or previous diagnosis; (6) cognitive or physical changes that prevent performance of the tests; and (7) initiation of another form of physical training during the intervention period.

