### Interventions

#### Intervention Program

Participants will complete 12 training sessions (twice weekly) spread over 7 weeks. The first week will be devoted to familiarization with the exercise protocol, while the subsequent 6 weeks will correspond to the actual intervention phase. Assessments will be conducted at baseline, immediately after the intervention is completed, and at a 4-week follow-up. The 4-week follow-up is included to evaluate the short-term maintenance of physical and psychological effects after the intervention; however, this timeframe does not allow conclusions regarding the long-term sustainability of behavior and psychological changes.

The groups will receive the designated intervention according to the following allocations: HBG, FxF, or CG. The 2 interventions will be compared to estimate the magnitude of differences in symptom relief and other outcomes, rather than to formally test equivalence. Participants allocated to the CG will be instructed to maintain their usual lifestyle and PA habits throughout the 7-week intervention period and the 4-week follow-up, and not to start any new structured exercise program (eg, supervised gym training, personal training, online exercise programs, or new exercise routines performed ≥2 times/wk). CG participants will receive no supervised training sessions or exercise prescription during the study period. To monitor potential contamination, all participants (including CG) will be asked at baseline, postintervention, and follow-up whether they started, stopped, or substantially changed their PA routines during the study. In addition, CG participants will be contacted weekly by message or phone call to confirm that no new structured exercise program was initiated and to record any relevant changes in PA behavior. Any initiation of a new structured exercise program during the trial will be documented and reported. These participants will remain in the intention-to-treat (ITT) analysis, and a per-protocol sensitivity analysis excluding participants with major protocol deviations will be conducted.

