#### Secondary Outcome Measures

Secondary outcomes will include analyses of the HADS subscales (HADS-A and HADS-D), sleep quality assessed using the Pittsburgh Sleep Quality Index (PSQI), mood states assessed using the Brunel Mood Scale (BRUMS), quality of life assessed using the World Health Organization Quality of Life–BREF (WHOQOL-BREF), and self-efficacy assessed using the Physical Exercise Self-Efficacy Scale. Physical function will be assessed using the 6MWT, handgrip strength, and the 5-repetition sit-to-stand test. Adherence will be evaluated according to group allocation: attendance at supervised sessions for the FxF group, and, for the HBG, aerobic exercise recorded via the Strava smartphone app (Strava, Inc) and resistance training reported via text message.

The PSQI, developed by Buysse et al [45], demonstrates high internal consistency (global Cronbach α=0.83). It consists of 19 questions assessing the quality and pattern of sleep, grouped into 7 components: subjective quality, latency, duration, habitual efficiency, disorders, medication use, and daytime dysfunction. Each component is evaluated on a scale of 0 to 3, yielding a global score (range 0‐21); a score ≥5 indicates poor sleep quality.

Mood states will be evaluated using the BRUMS [46]. Validated for the Brazilian population, the instrument shows robust psychometric properties, with subscale Cronbach α coefficients ranging from 0.70 to 0.85 (eg, tension α=0.78) [47]. It consists of 24 items across 6 domains: tension, depression, anger, vigor, fatigue, and mental confusion. Participants rate each item on a 5-point scale (0=“not at all” to 4=“extremely”), resulting in a total score ranging from 0 to 16 for each mood state.

Preoperative quality of life will be assessed using the WHOQOL-BREF instrument, developed by the World Health Organization [48]. Validated for the Brazilian population, the instrument demonstrates satisfactory internal consistency (Cronbach α=0.91) [49]. This self-assessment questionnaire consists of 26 items: 2 general questions regarding overall quality of life and health, and 24 items distributed across 4 domains: physical health, psychological, social relationships, and environment. The instrument enables a comprehensive, multidimensional assessment, in which higher scores indicate a better perception of quality of life.

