## Results

In August 2025, this clinical trial received funding from the Research Support Program of the UDESC. Participant recruitment and data collection are scheduled to begin in April 2026. Initial assessments and randomization are expected to occur between April and May 2026. The intervention phase is scheduled to be completed in September 2026, followed by data analysis between October and November 2026. Results are expected to be published in mid-2027.

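### All participants are awaiting bariatric surgery, yet no rule keeps surgery outside the roughly 11-week assessment window or records its date, so 4-week follow-up values may be postoperative

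*Protocol article*

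**What the plan says.** The Objective section of the abstract gives the target as effects "on physical and psychological variables in individuals with severe obesity awaiting BMS". Under Eligibility Criteria, every participant needs an indication for BMS and a "formal indication for preoperative physical therapy signed by the BMS surgeon". The one criterion on operations looks backwards: "history of previous BMS or abdominal or thoracic surgery within the previous year". The one exclusion that can apply after entry concerns exercise: "initiation of another form of physical training during the intervention period".

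Under Primary Outcome Measure the visits follow the program: "Assessments will be conducted before the start of the intervention, after the 7-week program, and at the 4-week follow-up". Intervention Program gives the reason for the last visit: "The 4-week follow-up is included to evaluate the short-term maintenance of physical and psychological effects after the intervention". The same section has all participants asked at each assessment about changes in physical activity, and controls contacted weekly about new exercise. Surgery is not among the events monitored.

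Statistical Analysis includes everyone randomized in a linear mixed model with group, time and their interaction over the three assessments, plus a per-protocol sensitivity analysis. Neither analysis mentions surgery.

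**The concern.** Surgery is the most foreseeable event after enrolment in this population, and the plan lets it fall between baseline and the last visit without a trace. A participant operated on in the weeks after the program would attend the 4-week follow-up as a recent surgical patient. The Hospital Anxiety and Depression Scale (HADS) score, sleep, quality of life, walk distance, handgrip and sit-to-stand time would then reflect the operation as well as the program, and would be read as maintenance of the program's effect.

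This reaches the primary outcome. The sample size and the model rest on the HADS group × time interaction over three time points, and the article singles out no one time point as primary. Follow-up values therefore feed the main test. Without surgery dates, the analyst cannot separate the two influences afterwards.

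**Working it through.** The plan gives no figure for this risk, so the check is mainly a comparison of the rules with the visit schedule.

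**1. Window.** 7 weeks of program + 4 weeks of follow-up = 11 weeks from baseline to last assessment.

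**2. Places where a rule on surgery could stand.**

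| Section | What it controls | Surgery between baseline and last visit |
|---|---|---|
| Eligibility, inclusion | Indication for BMS; signed physical therapy indication | No expected date or minimum wait |
| Eligibility, exclusion 4 | Surgery before entry | Not covered |
| Eligibility, exclusion 7 | New training during the intervention | Not covered |
| Intervention Program, monitoring | Physical activity changes | Not covered; no date recorded |
| Outcome Measures, timing | Visits relative to the program | Not linked to surgery |
| Statistical Analysis | All randomized; unspecified major deviations removed per protocol | Not named |

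The Secondary Outcome Measures section does say "Preoperative quality of life will be assessed using the WHOQOL-BREF instrument". This shows what is intended, but sets no condition on when a visit may take place or which values may be used.

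**3. Which visit is exposed.** The post-intervention assessment comes immediately after the program. The follow-up comes 4 weeks later, when the program no longer occupies the participant. The exposure is therefore mainly at the follow-up.

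**4. Size, under assumptions.** The documents give neither waiting times nor the effect of surgery on any outcome, so every input here is assumed.

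*Unequal frequency.* Bias in a between-arm contrast ≈ (difference in share operated on) × (shift due to surgery, in SD).

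| Difference in share | 0.3 SD | 0.5 SD | 0.8 SD |
|---|---|---|---|
| 0.05 | 0.015 | 0.025 | 0.04 |
| 0.10 | 0.03 | 0.05 | 0.08 |
| 0.20 | 0.06 | 0.10 | 0.16 |

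*Equal frequency.* If a share p in every arm is shifted by s SD, independently of the underlying score, the contrast is not biased but the variance becomes 1 + p(1 − p)s².
- p = 0.10, s = 0.5: 1 + 0.09 × 0.25 = 1.0225, so the SD rises by about 1%.
- p = 0.20, s = 0.8: 1 + 0.16 × 0.64 = 1.1024, so the SD rises by about 5%.

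If surgery also overrides the program's effect in those operated on, the contrast is diluted as well.

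**The case against.** The strongest reply is that this is an omission in a condensed article. The full protocol may contain the rule, the participant-flow and program figures cannot be seen here, and the text frames the study as preoperative throughout. Part of this stands: handling of individual assessments is often left to an analysis plan. But the article lists its eligibility criteria by number and describes its contamination checks in detail, including an exclusion for an event during the trial. Who is enrolled and which events are recorded are fixed in this text, and surgery is absent from both.

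A second reply is that keeping all values under intention to treat is a legitimate choice. That stands too. It is a reason to keep that model as primary, but not a reason to leave surgery unrecorded. The 30% dropout allowance, the per-protocol analysis and the possible multiple imputation do not help, because none identifies a postoperative value.

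A reader might infer more than the documents support:
- **Earlier surgery in the active arms, because they complete preoperative therapy.** The signed indication is required in all three arms, and no passage says that finishing the program triggers or speeds surgery. Dependence on arm is possible, not shown.
- **Equal contamination of the post-intervention visit.** Nothing in the documents points to surgery clustering before that visit.
- **A window well beyond 11 weeks, from the calendar in Results: "The intervention phase is scheduled to be completed in September 2026, followed by data analysis between October and November 2026".** These are trial-level dates. A baseline on 31 May plus 77 days ends on 16 August, so the calendar needs no longer window.
- **Exclusion 4 as proof that the plan regards testing after surgery as invalid.** No reason is given for that criterion; safety is equally plausible.

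**Conclusion.** The point holds, chiefly for the 4-week follow-up. As written, the plan admits postoperative values into the group × time model as evidence of maintained prehabilitation effects and collects nothing that would reveal them.

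The size cannot be determined from the documents. With long waits few participants are affected and the problem is small. With short waits it adds noise if surgery is equally frequent across arms, and bias if it is not. The range of 0.015 to 0.16 SD illustrates the unequal case and rests wholly on assumed shares and shifts; it is not an estimate for this trial. The gap is worth closing before recruitment, planned for April 2026, because unrecorded dates may be hard to recover later.

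**What to change.** - **Eligibility:** at screening, enrol only candidates whose BMS is not expected before their planned last assessment. Tie the wording to that visit rather than to a fixed number of weeks.
- **Data collection:** record the BMS date in all three arms. If surgery falls earlier than expected, do the next due assessment before it. The timing of surgery remains with the clinical team.
- **Analysis and reporting:** report by arm how many participants were operated on before each visit. Keep the intention-to-treat model as primary and add a HADS sensitivity analysis that excludes assessments made after BMS. That analysis relies on the missing-at-random assumption the plan already makes, which is one reason it should not replace the primary model.

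The cost is one eligibility line, one date field and a sentence or two on analysis. The downside is that a few candidates with early surgery dates become ineligible.

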**Figure 3. F3:**
[figure not shown]
Schematic drawing of the in-person and home-based prehabilitation program protocol.

The primary outcome will be the total score of the Hospital Anxiety and Depression Scale (HADS). The HADS was developed in England [43] and was validated for Brazilian Portuguese by Botega et al [44]; the instrument showed internal consistency (Cronbach α) of 0.68 for anxiety and 0.77 for depression in its validation study. The instrument is a scale completed through an interview, preferably answered by the patient, and contains 14 questions, of which 7 assess anxiety (HADS-A) and 7 assess depressive symptoms (HADS-D). The scale emphasizes the psychological signs or consequences of anxiety and depression, excluding clinical symptoms such as dizziness and headache. The questions alternate, with half of them written in a positive tone and the other half in a negative tone. Each question is assigned a score from 0 to 3, with 3 indicating a state associated with more depressive symptoms or anxiety. Analyses of the HADS-A and HADS-D subscales will be conducted as secondary exploratory outcomes. In this study, HADS scores ≥8 will be used as a cutoff for each domain, as this is the score that indicates the presence of depressive and anxious symptoms and possible cases of depression and anxiety.

#### Secondary Outcome Measures

Secondary outcomes will include analyses of the HADS subscales (HADS-A and HADS-D), sleep quality assessed using the Pittsburgh Sleep Quality Index (PSQI), mood states assessed using the Brunel Mood Scale (BRUMS), quality of life assessed using the World Health Organization Quality of Life–BREF (WHOQOL-BREF), and self-efficacy assessed using the Physical Exercise Self-Efficacy Scale. Physical function will be assessed using the 6MWT, handgrip strength, and the 5-repetition sit-to-stand test. Adherence will be evaluated according to group allocation: attendance at supervised sessions for the FxF group, and, for the HBG, aerobic exercise recorded via the Strava smartphone app (Strava, Inc) and resistance training reported via text message.

The PSQI, developed by Buysse et al [45], demonstrates high internal consistency (global Cronbach α=0.83). It consists of 19 questions assessing the quality and pattern of sleep, grouped into 7 components: subjective quality, latency, duration, habitual efficiency, disorders, medication use, and daytime dysfunction. Each component is evaluated on a scale of 0 to 3, yielding a global score (range 0‐21); a score ≥5 indicates poor sleep quality.

Mood states will be evaluated using the BRUMS [46]. Validated for the Brazilian population, the instrument shows robust psychometric properties, with subscale Cronbach α coefficients ranging from 0.70 to 0.85 (eg, tension α=0.78) [47]. It consists of 24 items across 6 domains: tension, depression, anger, vigor, fatigue, and mental confusion. Participants rate each item on a 5-point scale (0=“not at all” to 4=“extremely”), resulting in a total score ranging from 0 to 16 for each mood state.

Preoperative quality of life will be assessed using the WHOQOL-BREF instrument, developed by the World Health Organization [48]. Validated for the Brazilian population, the instrument demonstrates satisfactory internal consistency (Cronbach α=0.91) [49]. This self-assessment questionnaire consists of 26 items: 2 general questions regarding overall quality of life and health, and 24 items distributed across 4 domains: physical health, psychological, social relationships, and environment. The instrument enables a comprehensive, multidimensional assessment, in which higher scores indicate a better perception of quality of life.

To assess self-efficacy, the Physical Exercise Self-Efficacy Scale will be used [50]. This instrument consists of 5 items that assess an individual’s confidence in performing physical exercises under different emotional states. The items are as follows: feeling worried and in trouble, feeling depressed, feeling nervous, feeling tired, and feeling busy. The instrument was translated, culturally adapted, and validated for the Portuguese population by Martins et al [51]. The questionnaire can be self-administered or administered via interview. Each item is graded on a 5-point Likert scale, defined as follows: 1=“not true at all,” 2=“hardly true,” 3=“probably true,” and 4=“exactly true.”

The interviewer should take care not to influence the patient’s response. When a respondent does not understand the meaning of a question, the interviewer should reread the question slowly, without using synonyms, and neither the question nor its meaning should be discussed, nor should the answer scale be explained. In cases where this is impossible (illiteracy, severe visual impairment, or lack of clinical condition), the instrument is administered by the interviewer, and the effort to avoid influencing the individual’s answers should be redoubled. The score for each facet is the corresponding value marked, and the average of the items is used to obtain the score for each domain answered. The final score is calculated by averaging the scores of all domains (physical, psychological, social relationships, and environment) and ranges from 0 to 100 points. The higher the score, the better the quality of life in the domain or overall.

The 6MWT will be used to assess functional capacity, following the recommendations of the American Thoracic Society [52]. The procedure will be conducted by a trained evaluator in a standardized corridor at the university. Participants will be instructed to walk the longest distance possible for 6 minutes, receiving standardized encouragement. Heart rate, SpO₂, blood pressure, and subjective perception of exertion (perceived exertion using the Borg scale for dyspnea and lower limb fatigue) will be monitored at baseline, every 2 minutes, and at the end of the test. Continuous monitoring of heart rate and SpO₂ will be performed using a pulse oximeter. For greater reliability, each participant will perform 2 tests on the same day, with a minimum interval of 20 minutes between them. The longest distance covered will be considered for analysis.

Handgrip strength will be assessed using a Saehan DHD-1 digital dynamometer, following the recommendations of the American Society of Hand Therapists [53]. Participants will be seated comfortably in an armless chair with their feet flat on the floor, hips and knees flexed at approximately 90°, shoulders adducted and neutrally rotated, elbows flexed at 90°, forearms in a neutral position, and wrists in a range of 0° to 30° extension and 0° to 15° adduction. Three consecutive 3-second maximal contractions will be performed with each hand, with intervals of 30 seconds between attempts and 2 minutes between hands. The arithmetic mean of the 3 tests for each limb will be used for analysis.

The 5-repetition sit-to-stand test will be used to assess lower limb strength, balance control, fall risk, and functional capacity [54,55]. The participant will remain seated in a standardized chair, with feet flat on the floor and arms crossed across the chest, and will be instructed to stand up and sit down 5 consecutive times as quickly as possible. Before and after the test, heart rate, SpO₂, and perception of dyspnea will be recorded using the modified Borg scale. The total time to complete the test will be considered for analysis.

Adherence will be assessed based on the characteristics of each group. In the in-person group, attendance at supervised training sessions will be considered. In the HBG, adherence to aerobic exercise will be monitored by recording activities on the Strava app, while resistance training will be tracked using the Physitrack app (Physitrack PLC), which provides video and text instructions, automatic reminders, and self-monitoring functions. This tool has already demonstrated good acceptability in home-based programs and contributed to greater participant engagement [56]. Based on the records obtained, it will be possible to quantify the proportion of completed sessions relative to the total number planned, as well as verify training feedback and access to the health education videos. For analysis purposes, good adherence will be considered to be participation in at least 75% of the proposed sessions, a value close to that adopted in international multimodal prehabilitation programs that used more rigorous cutoffs, such as 80% [57].

Different approaches to measuring adherence across groups are justified by the distinct modes of intervention delivery. Adherence will be reported descriptively and explored in sensitivity analyses; no formal moderation analyses based on adherence are planned.

